#### Effectiveness outcomes

Health outcomes will be evaluated at baseline, at the end of the interventions (10 weeks) and 6-month follow-up. The primary effectiveness outcome will be current pain intensity, assessed in a one-dimensional aspect by the numerical rating scale (NRS) of 11 points, from 0 (no pain) to 10 points (the worst possible pain) [46]. The secondary effectiveness outcomes will be:*Pain:* the multidimensional aspect of pain will be evaluated by the Brief Pain Inventory [46]. The Brief Pain Inventory is a self-rated instrument and allows pain assessment in two dimensions: (1) pain intensity (items 3 to 6 of inventory); and (2) pain’s interference in the participant’s life (items 9a to 9 g of inventory). Each question has an NRS of 11 points, ranging from 0 (no pain/ no interference) to 10 (worst pain/ worst interference) and the average is used for each dimension.*Self-efficacy:* evaluated through the Chronic Pain Self-Efficacy Scale (CPSS) [51], with 22 items of individual’s beliefs, whose items are divided into three factors: (1) self-efficacy for pain control (AED); (2) self-efficacy for other symptoms (AES); and (3) self-efficacy for physical function (AEF). It is possible to obtain a score for each factor (score from 10 to 100), and the sum of all factors that range from 30 to 300 points. Higher scores demonstrate a greater individual’s ability to deal with the consequences of pain [51].*Function:* The Patient-Specific Functional Scale (PSFS-Br) will be used. The participant chooses 3 to 5 important activities in which they have greater difficulty due to their condition and then graduates the level of their difficulty on an 11 points scale, from 0 (inability to perform the activity) to 10 (capable of performing the activity at the same level as before the injury or problem) [52].*Sleep quality* will be evaluated by a self-rated sleep quality in the last 7 days on a scale of 0 to 100 points (0 – worst sleep quality; 100 – better sleep quality).*Health-related quality of life* will be evaluated using the EQ-5D-3L questionnaire, which is composed of a descriptive model with five health domains (mobility, self-care, usual activities, pain/discomfort, and anxiety/depression). Each domain has three response levels: ‘no problems’, ‘some problems’, and ‘extreme problems’. The instrument also has a visual analogue scale (EQ-VAS) for the self-rated health state which ranges from 0 (‘the worst possible health status) to 100 (‘the best possible health status’) [53, 54].*Prognostic stratification:* will be evaluated by the Keele STarT MSK Tool [55]. The tool contains 10 items (ranging from 0 to 12 points each) that, once scored, can place patients into three categories based on their risk of a poor outcome: (1) low risk (0–4 points); (2) medium risk (5–8 points); or (3) high risk (9–12 points).*Adverse events:* will be analysed by recording the number and type of adverse effects that occurred during the intervention period.

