### Data collection timepoints

We will evaluate participants at baseline, at the end of the intervention period (10 weeks), and 6 months after the randomisation. We will perform the evaluation through videoconference, telephone contact, or using an online questionnaire (e-mail or text message), according to the participant’s preference.

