**Fig. 3 Fig3:**
[figure not shown]
Adaptation of Proctor’s conceptual model of implementation research

The primary implementation outcomes will be cost-effectiveness, adoption, and acceptability (satisfaction using a numerical scale from 0 to 100). Primary and secondary implementation outcomes are described below and summarized in Table 1.*Acceptability* will be analysed from the perspective of the organisation through a focus group, from the perspective of end-users through an individual qualitative interview about satisfaction with the intervention, and by a numerical scale from 0 to 100 on how satisfied they were in participating in the intervention. The acceptability of the implementation will also be evaluated by the Acceptability of Intervention Measure (AIM) [47] in organisations and end-users. The AIM has four questions with a Likert scale from 1 (completely disagree) to 5 (completely agree), and the mean of the score will be used (1 to 5). Higher scores indicate greater acceptability [47].*Appropriateness* will be analysed from the end-users’ perspective regarding the perception of the appropriateness of each component of the *EducaDor* programme about their health condition through an adapted questionnaire [48]. This questionnaire will assess the degree to which participants agree with a series of statements about the intervention, on a Likert scale from 1 (totally disagree) to 4 (totally agree). The appropriateness of the implementation will also be evaluated by the Intervention Appropriateness Measure (IAM) [47] in the organisation and end-users. The IAM score is the same as the AIM.*Feasibility* will be evaluated from the perspective of the organisation and individual providers through a focus group, and the Feasibility of Intervention Measure (FIM) [47] will be used in participants, organisations and individual providers. The FIM score is the same as the AIM and AIM.*Adoption* will be analysed by the percentage of acceptance of public health users to participate in the *EducaDor* programme referred from primary healthcare. We will contact by telephone those public health users who refuse to participate by inviting them to an individual qualitative interview to identify barriers to engagement in the *EducaDor* programme.*Fidelity* will be evaluated by an independent pain specialist ([name]), who will randomly select 10% of the recorded meetings and evaluate the intervention providers in relation to the fidelity of the intervention manuals with the content and quality of the meetings in a qualitative individual interview.The adherence of participants with the *EducaDor* programme will be measured by the frequency rate in synchronous meetings; self-rated performance of proposed homework on a numerical scale from 0 to 10 during the intervention period; and by exercise adherence scale (EARS-Br) [49].*Penetration* will be analysed descriptively from the rate of public health users referred from each primary healthcare unit.*Sustainability* will be evaluated by a focus group with public health managers after the presentation of the results of the study to discuss the maintenance of the *EducaDor* programme, and by a response rate of synchronous group users and reasons for discontinuity of the programme through an individual qualitative interview.*Costs* will be estimated from the SUS and societal perspectives in a time horizon of 6 months. The SUS costs will include the intervention costs and healthcare utilization costs covered by SUS. The intervention costs will be determined by preparation, video recording, development and editing, maintenance and support technology costs, monitoring data costs and staff, training health professionals and project management costs, number and duration of phone calls and the number of text messages sent to participants. The e-book and asynchronous intervention costs will be diluted in 10 years. The healthcare utilization costs covered by SUS will include prescribed drugs, medical consultations, physiotherapy-based care, visits to specialists, diagnostic exams, emergency services and hospitalisation. The societal costs will include the SUS costs, private healthcare costs, patient costs (out-of-pocket expenses with unprescribed drugs, complementary costs, and transportation costs), and lost productivity costs (related to absenteeism). The quantities of resource utilization will be identified by the participants in a self-rated diary cost that will be provided at baseline and an assessor will collect this information by telephone every 3 months. The healthcare utilization costs covered by SUS will be valued using the Brazilian standard costs [50]. Patient costs will be valued using the out-of-pocket expenses reported by patients. Private transportation will be valued by the price of Brazilian gasoline per kilometre and public transportation by the reference price of Guarapuava city. The lost productivity costs will be estimated from the hours of absenteeism to work (paid and unpaid) through a questionnaire, and evaluated according to the Human Capital Approach and will be valued using gender-specific price weights [50].

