
**Table 1 Tab1:** Implementation outcomes

**Outcomes**	**Level of analysis**	**Indicators**		**Data Collection Tool**		**Time of data collection**
**Acceptability**	Organisation	Acceptability of the implementation		Qualitative interview and Acceptability of Intervention Measure (AIM)		Post-implementation
	Participants	Satisfaction with the intervention		Qualitative interview and 0 to 100 points scale and AIM		Post-implementation
**Appropriateness**	Participants	Are the components of the online pain science education programme appropriate for the health condition?		Qualitative interview, Intervention Appropriateness Measure (IAM) and an adapted questionnaire used by Liao et al. (2020)		Post-implementation
	Organisation	If intervention is appropriate for the public health condition		Intervention Appropriateness Measure (IAM)		Post-implementation
**Feasibility**	Participants	Feasibility of the intervention		Feasibility of Intervention Measure (FIM)		Post-implementation
	Organisation	Feasibility of the implementation		Qualitative interview and FIM		Post-implementation
	Individual providers	Feasibility of the implementation		Qualitative interview and FIM		Post-implementation
**Adoption**	Participants	Enrolled participants being contacted		Own domain database		During implementation
		Burden (reasons for not taking part)		Qualitative interview during triage		Pre-baseline
**Fidelity**	Creator of the intervention	10% of taped sessions of the intervention group were randomly selected and reviewed by an expert panel, against the full detailed intervention manuals for adherence and quality		Qualitative interview		Post-implementation
	Participants	Number of participants that adhered to the intervention		Frequency during intervention		During implementation
		Self-rated performing the proposed activities at home for 10 weeks and the 6-month of follow-up		Adherence to the proposed homework (0 to 10 points scale); and the exercise adherence scale (EARS-Br)		Post-implementation
**Penetration**	Organisation	Which primary healthcare units referred users with musculoskeletal pain for intervention?		Health regulation data and/or digital health record		During and post-implementation
**Sustainability**	Organisation	Do you think this project will be sustainable over time?		Qualitative interview		Post-implementation
	Participants	Indicator of drop in the response rate of the synchronous group		Own domain database		During implementation

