#### Physiotherapy-based care

All participants will receive physiotherapy-based care in one of the five physiotherapy centres accredited to SUS, according to the scheduling availability of the services. The physiotherapy-based care consists of 10 sessions, mainly based on exercises and electrophysical agents. Patients will be treated in an outpatient physiotherapy centre by independent therapists to minimize the possible preference bias of therapists.

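### Adverse events are recorded only during the 10-week intervention, although other health outcomes, adherence and costs are followed to 6 months; the window should be extended using contacts already planned

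*Protocol article*

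**What the plan says.** Protocol article, Effectiveness outcomes. The section opens with a general timing rule: "Health outcomes will be evaluated at baseline, at the end of the interventions (10 weeks) and 6-month follow-up". Adverse events come last in its list of secondary effectiveness outcomes and carry their own rule: "recording the number and type of adverse effects that occurred during the intervention period".

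Data collection timepoints. Participants are assessed at baseline, "at the end of the intervention period (10 weeks), and 6 months after the randomisation". The intervention period is therefore 10 weeks within a 6-month follow-up.

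Table 1, Fidelity, gives one indicator as "Self-rated performing the proposed activities at home for 10 weeks and the 6-month of follow-up", measured with a 0 to 10 homework scale and the EARS-Br. The text under Implementation outcomes describes the same homework scale as "self-rated performance of proposed homework on a numerical scale from 0 to 10 during the intervention period" and states no time limit for the EARS-Br.

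Physiotherapy-based care, given in all three arms: "The physiotherapy-based care consists of 10 sessions, mainly based on exercises and electrophysical agents". It is delivered "according to the scheduling availability of the services", with no weekly frequency and no end date.

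Implementation outcomes, Costs. The time horizon is 6 months. Resource use includes emergency services and hospitalisation. Participants keep a diary, and "an assessor will collect this information by telephone every 3 months".

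**The concern.** The adverse-event rule is narrower than the timing rule at the head of its own section, and narrower than the period over which the trial measures activity, pain, function and costs. It fixes what data are collected, so the gap cannot be closed at analysis: an event that nobody asked about cannot be recovered.

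A hospital admission in month 4 would enter the cost analysis but, under the stated rule, not the adverse-event outcome. The 6-month pain and cost-effectiveness results would then stand beside a harms result that covers 10 weeks. The programme aims at self-management, so the period after the last session matters for judging it.

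It is also unclear whether an event linked to a physiotherapy session held after week 10 would count.

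**Working it through.** The protocol gives no figure for adverse-event coverage, so there is none to reproduce.

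**Inputs**
- Adverse-event window: the intervention period (Effectiveness outcomes), 10 weeks (Data collection timepoints).
- Follow-up T: 6 months from randomisation. Taken as 26 weeks, with 24 weeks as a check.
- Physiotherapy: 10 sessions. Start week s and sessions per week k are not stated, so both are assumptions below.

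**Step 1. Share of follow-up outside the window** = (T − 10)/T
- T = 26: 16/26 = 61.5%
- T = 24: 14/24 = 58.3%

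**Step 2. Delay d from randomisation to programme start.** Allocation lists go out one week before the programme starts, which suggests some wait of unstated length. The total outside a 10-week window stays at 16/26, but the part after the programme is (26 − 10 − d)/26:
- d = 1: 15/26 = 57.7%
- d = 4: 12/26 = 46.2%

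The remainder, d/26, is waiting time before the start.

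**Step 3. Can physiotherapy outlast the window?** End week = s + 10/k

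| k (per week) | s (start week) | End week |
|---|---|---|
| 1 | 0 | 10 |
| 1 | 4 | 14 |
| 2 | 0 | 5 |
| 2 | 8 | 13 |

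Overlap beyond week 10 is possible on plausible schedules. The protocol does not state that it will occur.

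**Step 4. What the gap implies for events.** Let the rate after week 10 be r times the rate before it. The share of 26-week events falling after week 10 is 16r/(10 + 16r):
- r = 1: 16/26 = 61.5%
- r = 0.5: 8/18 = 44.4%

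These are illustrations only, because the protocol gives no event rate. They also ignore loss to follow-up, which the sample size section puts at 30%. The rate per person-week is a separate matter. With r = 1 the first-10-week rate equals the later rate, and with r = 0.5 it is twice the later rate. It would understate the later rate only if r exceeded 1, and nothing in the document shows that.

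**Step 5. Passages side by side**
- General rule for health outcomes: baseline, 10 weeks, 6 months. Adverse-event item in the same list: intervention period only.
- Home activity in Table 1: 10 weeks and the 6-month follow-up. Homework scale in the text: intervention period only.
- Emergency care and hospitalisation: collected over 6 months as costs. The article describes no link from these to the adverse-event outcome.

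**The case against.** The best defence is that this is a deliberate and reasonable choice. The intervention is education with low expected risk. All three arms share the same window, and all receive physiotherapy within a randomisation stratified by centre, so nothing points to bias between delivery modes. The opening sentence of Effectiveness outcomes is a general visit schedule. It includes baseline, which cannot apply to events during an intervention, so the specific rule can be read as overriding it. The SPIRIT schedule in Fig. 1 is not shown, and a fuller protocol may describe review of serious events.

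Much of this stands. It limits the point to a collection window that could cheaply be wider, and it rules out three stronger readings:

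- A reader might infer that nothing bearing on safety is recorded after week 10. That is not so: emergency visits, hospitalisations, pain, function and quality of life are all collected later, though not as adverse events.
- A reader might infer that home exercise is prescribed to 6 months. Table 1 measures home activity that far but does not prescribe it, and the text confines the homework scale to the intervention period.
- A reader might infer that the published harm rate would be too low. Step 4 shows that this does not follow. Only the 6-month count is incomplete.

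What the defence does not remove is the stated limit itself. It is a written rule, not an omission left to another document. Equal windows across arms do not supply the missing observations.

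**Conclusion.** The point holds as a cheap improvement. Adverse-event recording is confined to 10 weeks, while the trial's other health outcomes, its home-activity measure in Table 1 and its costs extend to 6 months. About 62% of follow-up (16 of 26 weeks; 58% on 24 weeks) has no planned adverse-event recording, so a 6-month count would be incomplete.

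These figures are shares of calendar time. They rest on reading the intervention period as 10 weeks, as Data collection timepoints states. The number and share of events missed are unknown, and physiotherapy after week 10 is possible rather than stated. No sample size, power, type I error or primary outcome depends on this point.

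**What to change.** 1. In Effectiveness outcomes, define the adverse-event window as randomisation to 6 months, reported separately for 0 to 10 weeks and for 10 weeks to 6 months. This also brings the item into line with the section's opening sentence.
2. Ask about adverse events, with the same question in every arm, at the existing 10-week and 6-month assessments and in the 3-monthly cost calls.
3. Screen each emergency visit and hospitalisation in the cost diary as a possible serious adverse event.
4. State how events linked to physiotherapy sessions after week 10 are counted.
5. Reconcile the text under Implementation outcomes with Table 1 on how long home activity is measured.

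The cost is a few sentences in the protocol and one added question at contacts that already take place. The downside is more unrelated events to classify, since people with chronic pain will report many over 6 months. Reporting the two periods separately keeps the 10-week result intact.

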
### The online pain science education programme (EducaDor)

The online pain science education programme (*EducaDor*) will be based on the model proposed by Reis et al. [56, 57]. The *EducaDor* programme will follow 10 steps that will be divided into videoconferencing meetings, videos, and e-book during the study: (1) acceptance; (2 and 3) pain education; (4) sleep hygiene; (5) pharmacological assistance; (6) recognizing stress and negative emotions; (7) increasing positive coping in lifestyle; (8) exercises; (9) communication; and (10) prevention of recurrence [56]. The content of these 10 pain science education steps also was written into an interactive e-book with simple writing and based on scientific literature.

Each chapter of the interactive e-book features a rich learning environment (texts, images, graphic schemes, podcasts, videos, and behavioural strategy activity) to provide a multisensory-training protocol and to produce greater and more efficient learning [58, 59]. Each chapter also contains behaviour strategies and activities for participants to develop during the week, to facilitate the comprehension of which changes that can be made in their daily life to have an impact on self-management and self-control of pain. All participants will receive the interactive e-book on their mobile phone, tablet or computer. It is expected that participants read and practice the activities and behavioural strategies, at least, one chapter per week.***1) Synchronous online group***

Participants will receive the interactive e-book of the *EducaDor* programme on their smartphone devices and e-mail at the beginning of the programme, and 10 synchronous online groups (one per week), in addition to physiotherapy-based care.

The synchronous online *EducaDor* programme will be held in groups of up to 12 participants, during 10 weekly synchronous meetings on the Whereby® platform on a date and time pre-established by the research group, which may be changed according to participants’ preferences. The meeting link will be available by text message and e-mail few minutes before the meeting time.

In the first meeting, we will also promote a conversation with the group to know about the health conditions of each participant, and their expectations with the programme and explore previous experiences regarding treatments received, phobias and beliefs about pain, injury and interventions. The professional will conduct each synchronous meeting with dialogued exhibition class, that is, there will be a presentation using multimedia material [57] shared on the computer screen and thus will be accessible for participant viewing on his computer, tablet, or smartphone during the meeting. At the same time, there will be an explanation about the topic of the meeting with the health professional. The professional will conduct the meetings using clear, objective, and assertive communication, aiming to promote reflection and behaviour change in the participants’ daily life. After the topic exhibition, participants will be encouraged to participate by exposing their doubts and/or sharing experiences.

Finally, the professional will accomplish the activity proposed in the respective chapter of the interactive e-book, and will make orientations for performing during the week.***2) Asynchronous videos group***

Participants allocated in the asynchronous videos group will receive the interactive e-book at the beginning of the programme and 10 videos (one per week) with the same topics of the synchronous online *EducaDor* programme sent on their smartphone devices and e-mail, in addition to physiotherapy-based care. Before receiving the materials, users will participate in an individual or group synchronous meeting of up to 12 participants on the Whereby® platform to receive a session of pain education, guidance for the use of the interactive e-book, and access to the videos over the 10 weeks. The videos were previously developed and tested in another clinical trial [60].***3) Interactive e-book group***

Participants allocated to this group will receive the interactive e-book of the *EducaDor* programme on their smartphone devices and e-mail, in addition to physiotherapy-based care. Before receiving the e-book, the users will also participate in an individual or group synchronous meeting of up to 12 participants on the Whereby® platform to receive a session of pain education, and guidance for the use of the interactive e-book over the 10 weeks.

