#### Fidelity of intervention delivery

The interventions will be conducted by four physiotherapy students ([name], [name], [name], and [name]) from Universidade Estadual do Centro-Oeste (UNICENTRO/Brazil). The team will receive 30 h of training regarding the interventions before the beginning of the *EducaDor* programme. The chief researcher of the study ([name]), who has 18 years of physiotherapy experience, will audit the online interventions once every month. To maintain the fidelity of the intervention delivery, the researchers will follow a structured manual of the *EducaDor* programme. All synchronous meetings will be recorded for further evaluation of the implementation fidelity.

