#### Sample size estimation

The sample size was estimated by simulation [61, 62]. The sample size simulation was performed in four steps: (1) defining the sample size problem and outcomes; (2) defining, writing and running the sample size simulation algorithm; (3) estimating the possible outcomes derived from the simulations; (4) finding the optimal sample size.

In step 1, the sample size problem was developed considering the following objective: to estimate the minimum sample size required to comply with a maximal type I error (*α*) of 0.05 or 5% and a maximal type II error (*β*) of 0.20 or 20%. The input outcomes were: populational mean pain intensity (0–10) of 6.0 with a standard deviation (SD) of 2.3; a hypothesised minimal clinically important difference (MCID) in pain intensity between groups of -1.0 with an SD of 0.25 [63]; three groups; three repeated measurements (baseline, 10 weeks and 6 months); a correlation within the repeated measurements of 0.30 or 30% [64]; a minimum of 30 participants per cluster (five physiotherapy facilities); a correlation within clusters of 0.20 or 20% [65]; and a loss to follow-up of 30% [66].

In step 2, the simulation algorithm was defined and written in R language [67]. The input outcomes defined in step 1 were then included in the algorithm. Normal distributions were simulated using the input means and SDs set in step 1 as hyperparameters. The simulations were gathered running the distributions considering several possible sample sizes for one group ranging from 5 to 5000 in 32 steps (i.e., 5 to 50 by 5; 60 to 100 by 10; 150 to 500 by 50; 600 to 1000 by 100; and 2000 to 5000 by 1000), with 100 replications for each step, and repeating this procedure 10 times (i.e., 10 iterations), summing up 32,000 sample size simulations in total.

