#### Quantitative data analysis

For continuous variables, we will calculate statistics of central tendency and dispersion, such as means and, standard deviation. For categorical variables, we will describe frequencies and absolute numbers. Normality will be investigated by visual inspection of histograms. The baseline characteristics of the participants and implementation outcomes will be calculated using descriptive statistics. The differences between groups and the 95% confidence interval will be calculated using mixed models. The fixed effect term will be composed of dummy variables indicating groups, and follow-up time-points, that is, 10 weeks and 6 months after baseline, and the interaction terms composed of group and time. The estimates will be adjusted for any potential differences that might exist at the baseline. The random effect term will be composed of: (1) a correlated random intercept and slope varying the intercept for the five physiotherapy clusters and varying the slope for time points; and (2) a correlated random intercept and slope varying the intercept for repeated measurements within each cluster and varying the slope for time-points [69].

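### The synchronous arm is taught in interacting groups of up to 12, but the mixed model has no teaching-group term, so intervals for synchronous contrasts will be too narrow if outcomes correlate within groups

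*Protocol article*

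**What the plan says.** **Delivery.** Under the heading for the EducaDor programme, the synchronous arm "will be held in groups of up to 12 participants, during 10 weekly synchronous meetings". The first meeting includes a group conversation about conditions, expectations and beliefs, and after each topic participants are invited to raise questions and share experiences. The video and e-book arms have one introductory meeting, held either individually or in a group of up to 12. Under Fidelity of intervention delivery, "The interventions will be conducted by four physiotherapy students".

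**Randomisation.** Under Procedures and randomisation, individuals are randomised in blocks, stratified by the five physiotherapy centres, so every centre contributes to the arms being compared.

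**Analysis.** Under Quantitative data analysis, between-group differences with 95% confidence intervals come from a mixed model with group, time and their interaction as fixed effects. The random part has two terms. The first is "a correlated random intercept and slope varying the intercept for the five physiotherapy clusters and varying the slope for time points". The second is a correlated intercept and slope for repeated measurements within each centre. Neither refers to the online teaching group or to the student who leads it.

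**Sample size.** Under Sample size estimation, the only clusters counted are the five physiotherapy facilities. The result is 105 per arm, 315 in total.

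**The concern.** People who meet weekly for ten weeks, hear each other's experiences and are taught together may end up with outcomes more alike than those of people in different groups. That correlation arises after randomisation, from the intervention itself, and mainly in one arm: a partially nested design. A model that treats synchronous participants at the same centre as independent then counts more information in that arm than it has.

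The model already allows for correlation from shared care at the physiotherapy centre. That term does not help here. Centre is balanced across arms by stratification, so its effect largely cancels in a between-arm contrast, while a teaching-group effect sits inside one side of the contrast.

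At stake are two of the three pairwise comparisons, synchronous versus video and synchronous versus e-book, for pain (the primary effectiveness outcome) and the other modelled effectiveness outcomes. Video versus e-book is little affected. Any positive ICC acts in one direction, towards overstated certainty about how synchronous delivery compares. The Discussion hypothesises that the synchronous and video modes will be the most cost-effective, so these contrasts matter to the conclusions.

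**Working it through.** **The plan's own figure.** The inputs under Sample size estimation are "populational mean pain intensity (0–10) of 6.0 with a standard deviation (SD) of 2.3"; a difference "in pain intensity between groups of -1.0 with an SD of 0.25"; type I error 0.05 (taken as two-sided; the article does not say); power 0.80; 30% loss.

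- Formula: n = 2 × (1.960 + 0.842)² × 2.3² / 1.0² = 83.04, so 84 per arm. The article's simulation gives 80, a point on its grid, where power is Φ(1 / (2.3 × √(2/80)) − 1.96) = 0.785. The two agree closely.
- From 80 to 105: 80 × 1.3 = 104, and 80 × (1 − 0.30²) / (1 − 0.30) = 80 × 0.91 / 0.70 = 104. Both land close to 105. Neither contains an allowance for teaching groups.

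**Number and size of groups.** 105 / 12 = 8.75, about nine groups. With 30% loss, 12 × 0.70 = 8.4, about 8 evaluable per group.

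**Formulas.** For teaching-group size m and ICC ρ, in the synchronous arm only:

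- design effect DE = 1 + (m − 1)ρ
- true SE / model SE for synchronous versus another arm of equal size = k = √((DE + 1) / 2)
- actual two-sided type I error = 2 × (1 − Φ(1.96 / k))

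The article gives no ρ. The values below are assumptions.

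| m | ρ | DE | k | Type I error |
|---|---|---|---|---|
| 8 | 0.02 | 1.14 | 1.034 | 5.8% |
| 8 | 0.05 | 1.35 | 1.084 | 7.1% |
| 8 | 0.10 | 1.70 | 1.162 | 9.2% |
| 12 | 0.02 | 1.22 | 1.054 | 6.3% |
| 12 | 0.05 | 1.55 | 1.129 | 8.3% |
| 12 | 0.10 | 2.10 | 1.245 | 11.5% |

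Using m = 8.4 instead of 8 gives 5.9%, 7.2% and 9.4%. At ρ = 0.01 the figures are 5.4% (m = 8) and 5.6% (m = 12).

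**Does adjusting for centre absorb it?** Simulated trials (4,000 per setting, 105 per arm, m = 12) were analysed with adjustment for centre and baseline and no teaching-group term. With groups mixed across centres, type I error was 8.4% at ρ = 0.05 and 11.9% at ρ = 0.10. With groups formed centre by centre it was 7.8% and 12.1%. The Monte Carlo standard error is about √(0.08 × 0.92 / 4000) = 0.4 percentage points. These match the formula, so centre adjustment does not remove the effect.

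**Power once the SE is right.** With 105 × 0.70 = 73.5 completers per arm, power for a 1.0-point difference is 0.75 ignoring teaching groups. With m = 8.4 it is 0.72, 0.68 and 0.62 at ρ = 0.02, 0.05 and 0.10.

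**The case against.** The best counter-argument is that the teaching-group ICC may be close to zero. Delivery is standardised by a structured manual, 30 hours of training, monthly audit and shared slides, and the primary effectiveness outcome is individual current pain, measured at 10 weeks and again at 6 months. This stands as a reason to expect a low ICC. It does not show that the ICC is zero, and the size of the problem has to be given as a range.

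A reader might infer several stronger things that the article does not support:

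- **That group membership is fixed and each group has one leader.** Neither is stated. What may change with participants' preferences is the date and time, and four students deliver the interventions without a stated assignment. Movement between groups would weaken the correlation.
- **That clustering exists in one arm only.** The video and e-book arms may share one introductory group meeting that includes a session of pain education. This is a much weaker source, but treating those participants as independent is a simplification.
- **That inference on satisfaction is affected in the same way.** Satisfaction is an implementation outcome, and Quantitative data analysis says that those are summarised descriptively. The point would reach it only if a between-arm interval were reported.
- **That the omission is simply left to an unseen analysis plan.** It is not: the article writes out the random effects, and the teaching group is not among them.

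A practical objection also stands. About nine groups give an imprecise variance component, and the model already carries correlated intercepts and slopes over only five centres, so a singular fit is a real risk.

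**Conclusion.** The point holds in conditional form. The stated model omits a source of correlation that the synchronous intervention can create, and the centre term cannot replace it. It would be too strong to say that the standard errors are too small. They will be too small for the two synchronous contrasts if the teaching-group ICC is above zero.

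Over assumed ICCs of 0.02 to 0.10, the true standard error is about 3% to 25% larger than the model's. With about 8 evaluable per group, which fits the planned 30% loss, the type I error is about 5.8% to 9.2%. Full groups of 12 raise this to about 6.3% to 11.5%, which is the upper end. At an ICC of 0.01 or 0.02 the effect is small.

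These figures assume equal arms, groups at or near full size before loss, stable membership, equal total variance across arms and independence in the other two arms. They apply to pain and the other modelled effectiveness outcomes.

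**What to change.** Record each synchronous participant's teaching group, and who led it, from the start. The meetings are scheduled by the research team and recorded, so this should be easy.

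In the analysis plan, replace the stated model with a partially nested one: add a random effect for teaching group that applies only in the synchronous arm (arm indicator × group), treat each participant in the other arms as a group of one, and use Satterthwaite or Kenward-Roger degrees of freedom. State in advance how the model will be simplified if the fit is singular, dropping the centre random slopes for time first and keeping the teaching-group term. State that the single introductory meeting in the other arms is taken as negligible clustering.

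The cost is a paragraph in the analysis plan and one extra identifier in the data. Intervals for the synchronous contrasts will be somewhat wider, and the teaching-group variance will be estimated from about nine groups. Resampling whole teaching groups in the economic bootstrap could be considered, but with about nine groups it is itself unreliable, so it is not part of the recommendation.

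If recruitment can still change, matching the precision of an unclustered 105 per arm needs 105 × (DE + 1) / 2 per arm: 117, 134 and 163 at ICC 0.02, 0.05 and 0.10 with groups of 12. Otherwise, report the achieved precision.
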